**Method:**

This study is a cluster randomised controlled trial of Year 2 classes from 54 primary schools across England. The schools will be randomly allocated into two groups to receive either an active intervention called Project Tomato, to support maintenance of fruit intake in Year 3 children, or a less active intervention (control group), consisting of a 5 A DAY booklet. Children's diets will be analysed using the Child And Diet Evaluation Tool (CADET), and height and weight measurements collected, at baseline (Year 2) and 18 month follow-up (Year 4). The primary outcome will be the ability of the intervention (Project Tomato) to maintain consumption of fruit and vegetable portions compared to the control group.

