### Sample size

From the nationally representative sample, a sub-set of schools will be recruited into the intervention trial. Cluster randomisation will be used, randomising at the school level, as the intervention will involve whole lesson plans and school-level policies. A sample of 25 children (one Year 2 class) from each school, will give a design effect of approximately 3.4 to take account of the cluster randomisation. To have 90% power to detect a 0.5 portion difference in fruit intake, 500 children per group are required, i.e. about 20 schools in each group. Based on results from our initial evaluation of the SFVS, 75% who completed CADET at baseline also completed the follow up CADET. To allow for this margin of safety, 27 schools per group will be selected in each group, i.e. 54 schools in total. The size of effect the study is powered to detect (one half of a portion of fruit/vegetable) was chosen because it was considered the smallest improvement in intake that was worthwhile detecting with an achievable sized sample, and considering the nature of the intervention.

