#### Behavioural

Children's attitude to fruit and vegetable consumption as measured by a set of ten questions embedded in CADET[14].

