### Statistical Analysis

A random intercepts model of child-level outcomes will be used allowing for the hierarchical structure of the data caused by cluster randomisation: child within school. An extra level for the class is unnecessary because only one class is included from each school. MLwiN[15] will be used for this analysis. The fixed effect for the intervention group will be included in the model as a single covariate.

Balance of school and child-level variables between the two intervention groups will be assessed at baseline. This will be carried out with the following variables i) at school level: percentage of children with English as an additional language, percentage of non-white children, percentage of children with free school meals eligibility and percentage defined as having special educational needs ii) and at child level: sex, age and each of the primary and secondary child-level outcomes.

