#### Children's attitudes

The ten items relating to children's attitudes to fruit and vegetables will be analysed using factor analysis to identify the underlying structure of their responses. Kaiser-Meyer-Olkin and Bartlett's test of sphericity will be used to assess the suitability of the data for factor analysis. Kaiser's criterion and scree plots will be used to determine the number of factors extracted. For each factor, internal consistency will be measured using Cronbach's alpha, as there will be a number of potential outcomes assessed with possibly more than one identified factor, this will be repeated at two time points. Then a multivariate analysis of variance will be performed to determine whether the intervention has a differential effect on children's attitudes over time.

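### The planned MANOVA of attitudes over time, read as a group-by-time test, compares change scores and is less precise than follow-up attitude adjusted for baseline; how much less depends on a correlation the protocol does not give

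*Protocol article*

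**What the plan says.** Under Secondary outcomes, Behavioural, the protocol article names as an outcome "Children's attitude to fruit and vegetable consumption as measured by a set of ten questions embedded in CADET". The Abstract places the two CADET measurements in Year 2 (baseline) and in Year 4, 18 months later. Under Study procedure, baseline data are collected before schools are told their allocation.

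The section Children's attitudes plans a factor analysis of the ten items and a check of internal consistency for each factor, and adds that "this will be repeated at two time points". It then states that "a multivariate analysis of variance will be performed to determine whether the intervention has a differential effect on children's attitudes over time". It does not name an interaction term, a baseline covariate or a school effect.

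The main Statistical Analysis section has a general rule: "A random intercepts model of child-level outcomes will be used allowing for the hierarchical structure of the data caused by cluster randomisation: child within school". On covariates it says: "The fixed effect for the intervention group will be included in the model as a single covariate".

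**The concern.** A test of whether the arms diverge between two occasions reduces to a comparison of follow-up minus baseline. With several factors it is Hotelling's T-squared on the vector of changes. A change score carries the noise of both measurements and fixes the coefficient of baseline at 1. When the true regression of follow-up on baseline is flatter than that, a chance baseline difference is over-corrected and precision is lost.

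Baseline attitude is measured before allocation is notified, so it is a proper pre-intervention covariate. Because the arms have equal expected baseline, follow-up adjusted for baseline estimates the same intervention effect. At stake is the precision of one named secondary outcome, for which the needed baseline value is already collected.

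**Working it through.** **The protocol's own figures.** None is given for attitude: no SD, correlation, effect size or power. The Sample size section concerns fruit intake, and its arithmetic from children to schools reproduces: 500/25 = 20 schools per group, and 20/0.75 = 26.7, hence 27. The design effect of 3.4 with 25 children per school gives an ICC of (3.4 − 1)/(25 − 1) = 0.10. That ICC is borrowed below for the clustered check.

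**Unclustered comparison.** Let r be the correlation between baseline and follow-up, with variance 1 at both times.

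- Change score: variance proportional to 2(1 − r).
- Follow-up adjusted for baseline: variance proportional to 1 − r² = (1 − r)(1 + r).
- Ratio, change to adjusted: 2/(1 + r). The standard-error ratio is its square root.

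The last column takes an effect for which the adjusted analysis has 90% power at two-sided 5%, and gives the change-score power as Φ(3.24 × √((1 + r)/2) − 1.96). The 90% is illustrative, since no power is stated for attitude.

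| r (assumed) | 2(1 − r) | 1 − r² | Variance ratio | SE ratio | Change-score power |
|---|---|---|---|---|---|
| 0.2 | 1.60 | 0.96 | 1.67 | 1.29 | 71% |
| 0.3 | 1.40 | 0.91 | 1.54 | 1.24 | 74% |
| 0.5 | 1.00 | 0.75 | 1.33 | 1.15 | 80% |
| 0.7 | 0.60 | 0.51 | 1.18 | 1.08 | 85% |
| 0.9 | 0.20 | 0.19 | 1.05 | 1.03 | 88% |

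A follow-up-only analysis has variance 1, so below r = 0.5 the change score is also less precise than ignoring baseline.

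**Clustered comparison.** A simulation used 20 schools of 25 children per arm, an ICC of 0.10 and separate child-level and school-level correlations. The adjusted model contained the child's baseline score and the school mean of baseline.

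- Both correlations 0.2 or 0.3: SE ratio about 1.24 to 1.26.
- School-level correlation 0.8, child-level 0.2 to 0.7: SE ratio about 1.05 to 1.09.

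**What the school mean contributes.** Take a child-level correlation of 0.2 and a school-level correlation of 0.8. The variance of a school mean splits into 0.10 (school) and 0.90/25 = 0.036 (child).

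- Change score: 2[0.10(0.2) + 0.036(0.8)] = 0.0976.
- Adjusted for the child's score only, slope near 0.2: 0.10(1 + 0.04 − 0.32) + 0.036(1 + 0.04 − 0.08) = 0.1066. SE ratio √(0.0976/0.1066) = 0.96, so no gain.
- Adjusted for the school mean as well: slope (0.10 × 0.8 + 0.036 × 0.2)/0.136 = 0.641, variance 0.136(1 − 0.641²) = 0.0801. SE ratio √(0.0976/0.0801) = 1.10.

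If school means are much more stable than individual children's scores, the gain therefore needs the school mean in the model.

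**The case against.** The strongest reply is that nothing here is stated wrongly. A comparison of changes is unbiased in a randomised trial and answers the question the section asks. The group-by-time reading is itself an inference, and a condensed article may leave the exact specification to a document not shown. Attitude is a secondary outcome with no stated power, so no figure in the protocol becomes wrong. A MANOVA also gives one joint test across factors, which separate models would lose.

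Most of this stands, and it limits the point to efficiency. It does not remove the point: the article commits to a particular method, and with equal variances and a common correlation at child and school level no r below 1 favours that method. The loss of the joint test is a real cost, and the fix has to deal with it.

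Two stronger readings are tempting. A reader might infer that the planned analysis is much less precise. The documents do not support that: they give no correlation, and a low one over 18 months in young children is plausible but assumed. A reader might also infer that the MANOVA ignores clustering and so inflates the type I error. With the fruit-intake design effect of 3.4 and clustering ignored, a nominal 5% test would run at 2[1 − Φ(1.96/√3.4)], about 29%. But the section does not say how school is handled, the general rule for child-level outcomes does include school, and 3.4 was not given for attitude. What can be said is that the MANOVA sentence leaves the school level out and should state it.

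**Conclusion.** The point holds as a moderate, avoidable loss of precision in a secondary analysis. Read as a group-by-time test, the MANOVA has a variance 2/(1 + r) times that of the baseline-adjusted analysis: a standard error about 29% larger at r = 0.2, 15% at 0.5, 8% at 0.7 and 3% at 0.9. It is material mainly if r is about 0.5 or below, and only about 5 to 9% in the simulated settings with a school-level correlation of 0.8.

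This rests on the group-by-time reading, on equal variances at the two occasions and on an assumed range for r. It is not a claim of bias.

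**What to change.** In Children's attitudes, replace the group-by-time MANOVA with the random-intercepts model of the Statistical Analysis section, fitted to each factor. The follow-up factor score is the outcome, the intervention group and the child's baseline score on the same factor are fixed effects, and school is the random intercept. Add the school mean of the baseline score as a further fixed effect, for the reason shown in the working. Score the factors with the same loadings at both times so that baseline and follow-up measure the same thing. Report the adjusted difference with its 95% confidence interval.

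If more than one factor is extracted, either keep a joint test of the intervention effect across factors through a multivariate multilevel model, or adjust for multiplicity.

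The cost is a few sentences of analysis wording. The data are already to be collected and multilevel software is already planned. A simple rule is needed for children with no baseline score, and the joint test takes slightly more modelling.

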## Discussion

This paper describes a cluster randomised controlled trial to investigate the effectiveness of flexible multi-component intervention designed to support the maintenance of fruit and vegetable consumption for Year 3 children in British primary schools. A positive result would identify methods and knowledge of how to maintain fruit and vegetable intake in young children, and will be useful for policies concerning the SFVS and public health initiatives. A negative result would be used to inform the research agenda and contribute to redefining future strategies for increasing children's fruit and vegetable consumption.

## Abbreviations

SFVS: School Fruit and Vegetable Scheme
